### Randomisation and blinding

Upon completion of baseline measures, participants are randomised to the intervention or the control group in a 1:1 ratio. A computer-generated random allocation sequence list (in blocks of two) is generated in Stata 13 (StataCorp LP, College Station, Texas, USA). To ensure allocation concealment to study personnel until group allocation, the allocation list is monitored by a member of the research group with no participant contact. After randomisation, participants receive an email containing information about their group allocation. Assessors of the primary and secondary outcomes are blinded to group allocation; however, due to the design of the study participants are not blinded to their allocation.

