### Statistical analyses

Trial evaluation will be performed with linear mixed model analyses using intention to treat principles. In the statistical models we will use time as a categorical variable (0, 3 and 6 months) with time 0 as a reference group and include an interaction between group and time. The dependent variable is post intervention scores for MVPA (i.e., minutes/day) and the secondary outcomes (e.g., active transportation (minutes/day)). Three-way interactions will be analysed in order to evaluate if the intervention effect was moderated by any of the baseline covariates (e.g., age, sex, educational attainment, neighbourhood walkability or health related quality of life). Missing values on baseline covariates and on follow-up assessments will be imputed simultaneously using multiple imputation with chained equations [m (number of imputations) = 20] [44] taking into account variables of importance for predicting the missing values (e.g., age, sex, country of birth, educational attainment, occupation, season for intervention (i.e., autumn or spring) etc.). Continuous variables will be imputed using predictive mean matching (5 nearest neighbours). Binary variables will be imputed using logistic regression, and multi-categorical variables will be imputed using ordinal logistic regression (if ordered) or multinomial logistic regression (if unordered). Descriptive data over adherence to the intervention will be presented. Per protocol analyses examining effects related to adherence to the intervention (e.g., number of registered days in the app, goals set and achieved) will be conducted using linear mixed models adjusting for age, sex, country of birth (Sweden/not Sweden), educational attainment, occupation and season for intervention. As in the primary analysis, time, group and time-group-interactions will also be included. Sensitivity analyses concerning deviations from the missing at random assumption will be performed using delta-adjustment [45]. Statistics Sweden will provide summary statistics for responders and non-responders regarding age, sex, country of birth, education level and area of residence. All *p*-values < 0.05 (two-sided) will be regarded as statistically significant.

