### Trial status

In June 2017, final modifications to TRavelVU Plus were made and in August 2017 the app content and usability was tested in a pilot study, with minor changes to the app being made thereafter. Recruitment of participants, baseline assessments and randomisation of participants started in September 2017 and will continue until April 2018. Outcome assessments at the end of the intervention will be finalised by July 2018. Follow-up assessments (six months after randomisation) will be finalised in October 2018.

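### The primary mixed model, as described, has no season-by-time term; prespecifying one would give a small, nearly free gain in precision

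*Protocol article*

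**What the plan says.** The Statistical analyses section of the protocol article sets up a linear mixed model: "In the statistical models we will use time as a categorical variable (0, 3 and 6 months) with time 0 as a reference group", with a group-by-time interaction. It names no adjustment covariate for this model.

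Season appears twice in the same paragraph. It is one of the predictors in the multiple imputation ("season for intervention (i.e., autumn or spring) etc"), and it is one of six adjustment variables in the per-protocol models ("adjusting for age, sex, country of birth (Sweden/not Sweden), educational attainment, occupation and season for intervention"). The next sentence states what those models share with the primary one: "As in the primary analysis, time, group and time-group-interactions will also be included".

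Two design facts bear on this. Under Trial status, recruitment and randomisation "started in September 2017 and will continue until April 2018". Under Randomisation and blinding, "A computer-generated random allocation sequence list (in blocks of two) is generated in Stata 13", and each participant is randomised after completing their own baseline measures. No stratification factor is named.

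**The concern.** A participant randomised in September is measured again in December; one randomised in April is measured again in July. The intervention works through walking and cycling, so it is plausible that the underlying 3-month change in MVPA differs between these cohorts. A model with a single time effect for everyone cannot fit that difference, and it goes into the residual variance.

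Blocks of two pair participants who are adjacent in the allocation list, so the arms are nearly balanced over calendar time. Season then adds little or nothing to the true sampling variation of the group difference, while an analysis that ignores it counts it as noise. The standard error comes out somewhat too large, and the confidence interval for the primary effect is wider than it need be. Precision is all that is at stake.

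**Working it through.** **Inputs from the article (Sample size and power considerations; Statistical analyses).** 100 completers per arm, target difference 10 min/day, SD 25 min, two-sided α = 0.05.

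**Assumptions, not in the article.** Correlation of 0.6 between baseline and 3-month MVPA (range 0.5 to 0.7); two equal season cohorts whose 0-to-3-month change deviates by ±d from the average.

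**1. The plan's own figure.** Standard error = 25 × √(2/100) = 3.54. Normal-approximation power = Φ(10/3.54 − 1.96) = 80.7%; the t-test gives 80.4%. The stated 80% is reproduced with no season adjustment. Enrolment of 200/0.8 = 250 also reproduces.

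**2. Variance of the change.** Within season: 2 × 25² × (1 − 0.6) = 500, so SD = 22.4. Leaving season out adds d², so the standard error is multiplied by √(1 + d²/500). Power is for a t-test with 100 per arm and a difference of 10.

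| d (min/day) | Variance | SE of difference | SE too large by | Power |
|---|---|---|---|---|
| 0 (season modelled) | 500 | 3.162 | – | 88.2% |
| ±2.5 | 506.25 | 3.182 | 0.6% | 87.9% |
| ±5 | 525 | 3.240 | 2.5% | 86.7% |
| ±10 | 600 | 3.464 | 9.5% | 81.9% |

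With correlation 0.5 or 0.7 the within-season variance is 625 or 375. At ±5 the standard error is then 2.0% (√(1 + 25/625)) or 3.3% (√(1 + 25/375)) too large.

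**3. These power losses are, if anything, upper limits.** The table treats season as adding to sampling variation. With exact balance it does not: at ±5 the estimate still varies with SE 3.162, while the unadjusted test uses 3.240. Power is then about Φ((10 − 1.97 × 3.240)/3.162) = Φ(1.14), or 87.3%. Under the null, the unadjusted test rejects slightly less often than 5%: 4.4% in a simulation of paired allocation at ±5.

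**4. Which term helps.** Baseline is one level of the outcome, so a constant season shift cancels from the change. A simulated random-intercept model (100 runs, 200 participants, blocks of two in calendar order, complete data, correlation 0.6, ±5 in the 3-month change) gave these mean standard errors for the 3-month group-by-time term:
- no season term: 3.193
- season main effect: 3.193
- season by time: 3.145, which is 1.5% smaller

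The point estimate was the same in all three. The gain is below the 2.5% in the table because this model pools its residual variance over three visits and the season effect was placed at only one of them.

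**The case against.** The strongest reply is that nothing here is wrong. An unadjusted group-by-time mixed model is a valid primary analysis. The article never says that the model contains only these terms, and a fuller covariate list may sit in an analysis plan that is not shown. That stands in part. The absence of covariates is inferred, but it is the natural reading, because the same paragraph lists covariates for the imputation and per-protocol models and none for the primary model.

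It is also fair that the size is assumed. The ±5 case already means a gap of 10 min/day between cohorts, equal to the whole target effect. September and April starters are the two ends of the recruitment window, and those in between may differ less.

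A reader might go further and infer any of three stronger points, which the article does not support:
- **A serious loss of power.** The ±10 case needs cohorts 20 min/day apart in their change, twice the target effect, and nothing in the article suggests this. Even then, unadjusted power is 81.9%, above the planned 80%.
- **A fault in having season in the imputation model but not in the primary model.** Extra predictors in multiple imputation are ordinary practice; the trouble comes when the imputation omits terms that the analysis uses.
- **An inconsistency between the intention-to-treat and per-protocol adjustment sets.** Per-protocol comparisons depend on adherence after randomisation and need adjustment for confounders; the randomised comparison does not.

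**Conclusion.** The point holds as a modest improvement in efficiency, not as an error. If the 3-month change in MVPA differs by season of start, the primary model as described gives a standard error that is somewhat too large. For an assumed deviation of ±2.5 to ±5 min/day the excess is about 0.6% to 2.5%, and power is 87.9% to 86.7% against 88.2%. This rests on an assumed season effect, a within-person correlation of 0.6, equal season cohorts and a primary model with no covariates. The estimate is unbiased, the type I error is at or slightly below its nominal level, and the sample size reaches its stated power without adjustment. The change is still worth making, because the plan itself treats season as relevant, the variable is already coded and the design balances it.

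**What to change.** State in the analysis plan, before outcomes are examined by arm, that the primary mixed model includes season of start and its interaction with time, alongside group, time and group by time. Keep the model without season as a sensitivity analysis. A season main effect alone is not enough.

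The autumn/spring code is the simplest choice: one main effect and two interaction terms. Month of randomisation should recover more if change varies within a season, but it costs more. September to April is eight months, so a categorical version needs 7 main-effect and 7 × 2 = 14 interaction terms; a smooth function of calendar time would need fewer.

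No new data are needed. The cost is a sentence of wording and, with the binary code, a few degrees of freedom. If the sponsor prefers the unadjusted model, a statement that this is deliberate would settle the point.

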### Trial status

In June 2017, final modifications to TRavelVU Plus were made and in August 2017 the app content and usability was tested in a pilot study, with minor changes to the app being made thereafter. Recruitment of participants, baseline assessments and randomisation of participants started in September 2017 and will continue until April 2018. Outcome assessments at the end of the intervention will be finalised by July 2018. Follow-up assessments (six months after randomisation) will be finalised in October 2018.

## Discussion

The SCAMPI trial aims to evaluate the effectiveness of a 3-month behaviour change program delivered via a smartphone app to promote active transportation (i.e., walking and cycling) in adults aged 20–65 years. Active transportation has great potential to increase physical activity levels and thus influence the health of many people; however, interventions targeting travel behaviours are few. To the best of our knowledge, SCAMPI is the first study to assess a smartphone app to deliver such an intervention.

The SCAMPI study has many strengths, including the randomised controlled design and the relatively large population based sample. This design will enable us to assess travel behaviour and intervention effectiveness in a heterogeneous sample representing both urban and non-urban areas in the Stockholm County. Furthermore, the use of objective measures for both physical activity (accelerometers) and travel behaviour (TravelVU app) will provide unique data extending previous research on this topic that have been limited to self-reported data [46]. The novelty of SCAMPI is the development of a smartphone app including a behaviour change program to support participants to engage in active transportation. To date, we found one prior study using an app to promote active transportation as part of a larger campaign; however, the web based app in that study targeted a selected population and used a non-randomised design that did not enable the effectiveness of the app to be assessed [20]. The urgent need to find effective solutions to decrease the alarmingly high levels of sedentary behaviour among adults makes the focus on active transportation valuable. Active transportation may be an attractive option for people to accumulate physical activity time in their everyday life, who otherwise would be inactive. The TRavelVU Plus app therefore has the potential to make a difference on health outcomes for those in greatest need of this change.

The behaviour change program is anchored in the Social Ecological Theory and the Social Cognitive Theory. A theoretical approach not only guides the intervention developers to appropriate trial content, but has the advantage of making the intervention easier to replicate if found effective [47]. Theoretical frameworks are also recommended to make interventions more effective [47, 48]. A further strength of the behaviour change program is the use of several behaviour change techniques from different theoretical domains [28]. To include a variety of intervention functions and behaviour change techniques have been associated to intervention success [49, 50]. Specifically, ‘self-monitoring of behaviour’ and ‘intention formation’ have proven valuable in interventions that promote active transport, such as cycling and walking [49, 51]. Furthermore, the intervention was developed using key psychological theories and behaviour change strategies known to positively influence physical activity [52, 53].

Limitations of the trial are that we were unable to individually tailor messages due to budget constraints; a feature that has been associated with higher participant engagement [30]. While the objective assessment of travel behaviour in both groups is a strength of this study, participants in the control group will be aware of their travel behaviours through the TRavelVU app, which may have an effect on their behaviour and thus may dilute the effect of the intervention. Finally, a technical consideration that may be a limitation for some users is battery consumption on their smartphones when using the app.

We chose to recruit our population from a random sample of the general population, using letters sent out by Statistic Sweden, which we have successfully used previously [32, 54]. We believe that we thereby obtain a heterogeneous sampling frame of participants, enabling us to examine the intervention effect among participants with various characteristics. It is possible that this study attracts those who are already physically active and thus the intervention effect may be reduced. However, with the chosen design we have the opportunity to reach a large sample and to test the usability of the app in an appropriate manner before extending the use of the app to other populations. In the future, possible arenas for implementation of the app are municipalities wanting to improve public health in the general population. Thus, we are evaluating the app in the same context as it will be delivered.

Active transportation is cheap, easy-to-use and can become a daily habit for many people. Thus, if the TRavelVU Plus app is effective it has potential to offer a low-cost intervention that can be delivered at scale to promote active transportation. Active transportation can significantly contribute to increasing physical activity levels and thus improve the health of many and thereby decrease related societal health care costs.

## Abbreviations

App: Application
BCT: Behaviour change techniques
mHealth: Mobile health
MVPA: Moderate-to-vigorous intensity physical activity
NEWS: Neighbourhood environment walkability scale
SCAMPI: The Smart City Active Mobile Phone Intervention
TDF: Theoretical domain framework
TPAQ: Transport and physical activity questionnaire
